### Sample size

We assumed a medium effect size (0.5) to be a clinically relevant difference in patients’ satisfaction between the two study groups. Using a power of 0.8 and an alpha less than 0.05, at least 64 patients per study group are required. Accounting for an estimated dropout of 15%, 75 participants in each group are needed.

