**Methods:**

We will conduct a multicentre, two-arm randomised controlled trial in The Netherlands. We plan to include 150 patients who will be treated with curative intent for either breast, lung, colorectal, gynaecologic cancer, or melanoma. Further inclusion criteria are: age 18 years and older, able to answer questionnaires in Dutch, GP agrees to participate and the possibility to include the patient before the start of treatment. All patients receive care as usual. The intervention arm will receive additional structured follow-up consisting of a GP consultation before onset of treatment to empower the patient for shared decision making with the specialist and a minimum of three contacts with the HON during and after treatment. Primary outcomes are: patient satisfaction with care at the level of specialist, GP and nurse and healthcare utilization. Secondary outcomes include: quality of life, employment status, patient empowerment, shared decision making, mental health and satisfaction with given information. Repeated questionnaires, filled in by the participants, will be assessed within the 1-year study period.

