### Outcomes

The primary outcomes are patient satisfaction with care and health care utilization. Secondary outcomes are health related quality of life, employment, patient empowerment, shared decision making, mental health and satisfaction with information.

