### Primary outcome

To determine the primary outcome parameters the following validated questionnaires will be used: European Organisation for Research and Treatment of Cancer Satisfaction with care questionnaire (EORTC-IN-PATSAT32) [21], a Numeric Rating Scale (NRS) and the Medical Cost Questionnaire of the institute for Medical Technology Assessment (iMTA MCQ) [19, 22]. EORTC-IN-PATSAT32 consists of 32 questions and measures patients’ appraisal of hospital doctors and nurses, as well as aspects of care organisation and services [21]. The questionnaire will be adjusted to specify the satisfaction on specialists, GP and nurses. The NRS has a scale from 0 to 10 with the following question “How satisfied are you with the received care?”. Herein 0 implies “not satisfied at all” and a 10 implies that the patient “could not have been more satisfied” with the received care. The iMTA MCQ contains 31 questions and measures healthcare utilization (specific to the Dutch situation) [22]. The questionnaire will be adjusted to differentiate between the use of supportive care in primary or secondary care settings. Furthermore, questions evaluating medication use will be removed and questions evaluating the use of online websites and tools will be added. In addition, patients’ health records will be used to assess health care consumption.

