### Statistical analyses

All analysis will be performed following the intention-to-treat principle. Baseline characteristics will be shown by calculating means or medians for continuous variables and frequencies or percentages for categorical variables. Characteristics of patients who complete the study and patients who drop out, will be compared using T-tests for continuous variables and Pearson’s Chi-square analyses for categorical variables.

Linear regression analyses will be used for continuous variables adjusted for baseline variables (if measured at baseline) and treating hospital and cancer type. Mixed linear regression modelling adjusted for baseline variables as fixed factors (if measured at baseline) and stratification factors (treating hospital and cancer type) will be used to compare outcomes on repeated follow-up measurements T3 and T5. In these longitudinal analyses, the statistic model accounts for missing data based on the observed data [31]. Differential intervention effects due to sex (men/women), age (≤65/> 65 year), personality of type D (defined as 'scoring high on negative affectivity and social inhibition' [32]) (yes/no), type of cancer (breast/lung/colorectal/gynaecologic/melanoma), co-morbidity (none/1–2/> 3) and baseline levels of the outcomes of interest will be explored by adding interaction terms to the regression model.

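### Two primary outcomes are named, one of them split into several scores, but the sample size and its 80% power cover a single unnamed satisfaction comparison at the full 0.05

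*Protocol article*

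**What the plan says.** The Outcomes section states: "The primary outcomes are patient satisfaction with care and health care utilization". The Aim and the Discussion name the same two domains and rank neither above the other.

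The Methods part of the Abstract is more detailed: "Primary outcomes are: patient satisfaction with care at the level of specialist, GP and nurse and healthcare utilization". The Primary outcome section explains the split by provider, which comes from adapting the EORTC-IN-PATSAT32: "The questionnaire will be adjusted to specify the satisfaction on specialists, GP and nurses". The same section lists a second satisfaction instrument for the primary outcome: "The NRS has a scale from 0 to 10 with the following question" about the care received. Utilisation is measured with an adapted iMTA MCQ and from health records.

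The Statistical analyses section describes linear regression, and mixed linear models "to compare outcomes on repeated follow-up measurements T3 and T5". It gives no test level and no order among the primary outcomes, and it names no leading score or time point.

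The Sample size section assumes a standardised difference of 0.5 in patients' satisfaction and concludes: "Using a power of 0.8 and an alpha less than 0.05, at least 64 patients per study group are required". With 15% dropout this becomes 75 per group. Utilisation is not mentioned there.

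**The concern.** The power statement and the set of primary outcomes do not match. The calculation spends the whole 0.05 on one satisfaction comparison and does not say which satisfaction score, or which time point, it refers to. The second primary outcome has no effect size and no power.

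Two things are at stake. If several primary results are each read at 0.05, the chance of at least one false-positive primary finding exceeds 5%. If alpha is divided to prevent this, the planned numbers no longer give 80% power. The trial is unblinded and satisfaction is self-reported, so leaving open which score carries the confirmatory claim is a real weakness.

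**Working it through.** **Inputs from the Sample size section:** d = 0.5 (satisfaction only), alpha 0.05, power 0.80, 64 per group, 15% dropout, 75 per group. Sidedness is not stated.

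**Assumptions not in the documents:** the number of primary tests, the correlation between them, the rule that any one success counts, and, where needed, d = 0.5 for utilisation. Ranges are shown for the number of tests and the correlation.

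**1. Reproducing the plan's figure.** Normal approximation: n = 2(1.960 + 0.842)² / 0.5² = 62.8, so 63 per group. The two-sample t-test needs 63.77, so 64, with power 80.1%. A one-sided test would need only 50 to 51, so the calculation was two-sided. For dropout, 64/0.85 = 75.3, and 75 × 0.85 = 63.75, so 75 is a rounding matter of no consequence. The stated size is therefore right for exactly one two-sided test at 0.05.

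**2. Counting the primary tests.** The Outcomes section gives two. The Abstract gives four if providers are counted separately (specialist, GP, nurse, utilisation). Adding the rating scale from the Primary outcome section gives five.

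**3. Family-wise error if each is tested at 0.05 and any one success counts.** For independent tests it is 1 − 0.95^k. For correlated tests it comes from a simulation of equicorrelated normal statistics (1,000,000 draws).

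| Tests | Independent | Correlation 0.5 | Correlation 0.9 |
|---|---|---|---|
| 2 | 9.75% | 9.1% | 7.0% |
| 4 | 18.5% | 15.5% | 9.3% |
| 5 | 22.6% | 18.2% | 10.1% |

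**4. Power if alpha is split equally.** Approximately Φ(d√(n/2) − z) with z the two-sided critical value at 0.05/k. At n = 64, d√(n/2) = 0.5 × √32 = 2.83. The table gives t-test values, and the n needed for 80% power before and after 15% dropout.

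| Tests | Alpha each | Power at 64 per group | n per group for 80% | With dropout (total) |
|---|---|---|---|---|
| 1 | 0.05 | 80% | 64 | 75 per group as stated (150) |
| 2 | 0.025 | 71% | 78 | 92 (184) |
| 4 | 0.0125 | 62% | 91 | 108 (216) |
| 5 | 0.01 | 59% | 96 | 113 (226) |

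Even if all 75 per group were evaluable, power would be 79% at 0.025 and 67% at 0.01.

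**5. Holm with two tests.** Satisfaction is significant if its p-value is below 0.025, or if it is below 0.05 and utilisation is below 0.025. The floor is therefore 71%. With d = 0.5 on both outcomes and independent tests, power is 0.712 + (0.801 − 0.712) × 0.712 = 0.775 from these rounded values, or about 78% before rounding.

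**6. If both outcomes had to succeed.** Alpha would hold at 0.05. With d = 0.5 for both, joint power would be 0.801² = 64% if independent and about 74% at correlation 0.8.

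**7. Fixed sequence.** With one named satisfaction score first at 0.05 and utilisation tested only if it succeeds, family-wise error stays at 5% and the first test keeps its 80%. Power for utilisation remains unknown.

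**The case against.** The strongest reply is that the figure of 64 is not wrong, and that an article may leave testing order and multiplicity to a full protocol or analysis plan that is not shown. This largely stands as far as the missing multiplicity rule goes. It does not remove the mismatch. The article itself fixes two primary outcomes and fixes the sample size on one comparison at the whole 0.05. A later plan can choose an order, but with 64 per group it cannot restore the calculated 80% under a split alpha, and the sample size statement gives utilisation no power basis. Adjustment for baseline could recover some power, but the calculation does not use it.

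Several stronger readings are tempting, and the article does not support them:

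- *Either the error rate or the power must fail.* Not so: the fixed sequence in step 7 keeps both for the first test.
- *Any one positive score will be declared a primary success.* No such rule is written. The error rates above are conditional on it.
- *There are ten tests, because T3 and T5 are both read.* A mixed model over repeated measurements can give one treatment effect, so doubling the count is not justified.
- *The 64 per group was computed for the rating scale at 12 months.* The Sample size section names neither an instrument nor a time point.
- *Controls cannot rate a GP, so the provider scores are not comparable.* The Control group section calls primary care guidance unstructured, not absent, and describes nurses in the hospital team. The adapted questionnaire is not shown.

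**Conclusion.** The point holds in a limited form. The sample size arithmetic is correct, but the power statement covers one unnamed satisfaction comparison while the protocol gives two domains equal primary status and measures one of them in several ways. The 80% power at 0.05 therefore does not hold for the primary set as written.

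For the two named outcomes, the cost is a family-wise error of about 7–10% or a fall in power from 80% to 71%. If four satisfaction measures and utilisation are counted separately, it is about 10–23% or a fall to 59%. The error figures assume tests at 0.05 with any one success counting, and correlations from 0.9 down to independence. The power figures assume an equal split, d = 0.5 and 64 evaluable patients per group. Neither loss is inevitable, and the planned number of patients need not change.

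**What to change.** Before outcomes are analysed:

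1. Name one satisfaction score and one time point or model contrast as the first primary test at two-sided 0.05. The overall rating scale at T5 is one possible choice. It would be a new decision, not something the Sample size section implies. Confirm from the questionnaire schedule that the scale is collected then. Under Data collection, patients who finish primary treatment before T3 receive the T5 questionnaires three months after the T3 set, so for them T5 falls before 12 months. The definition should say so.
2. Test utilisation second in a fixed sequence, only if the first test succeeds.
3. Report the specialist, GP and nurse scores as secondary.
4. State in the Sample size section that the 80% power applies only to the first test.

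If both domains must stay co-primary, use Holm and restate power for satisfaction as at least about 71%, with power for utilisation unknown.

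The cost is wording only, with no extra patients. The drawback is that fewer results can carry the primary label, and in a fixed sequence utilisation cannot be claimed as confirmed if the satisfaction test fails.

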## Discussion

The aim of the GRIP study is to assess the effects of structured follow-up from primary care after the diagnosis of cancer on satisfaction and healthcare utilization of patients treated with curative intent. To optimise personalised cancer care for a growing patient population and for effective implementation of structured follow-up from primary care, policymakers and professionals need more information on the effects of structured and continuous primary care involvement in the cancer continuum. The GRIP study will provide evidence on the effects on patient satisfaction and healthcare utilization and secondary outcomes. In this pragmatic study, patients with multiple cancer types will be included aiming at high generalizability of the results. It will be explored whether there are subgroups of patients for whom this structured primary care works best.

In this protocol some choices were made, that need clarification. First, we chose to assess the addition of structured follow-up from primary care by a GP and HON to care as usual instead of substitution of the supportive care provided in hospitals. This choice was made because we believe it is not feasible nor desirable to completely replace supportive care provided from secondary care by that from the primary care team. In addition, we aim to test the assumption that additional care from primary care will lead to a shift of the utilised care from the secondary to the primary care setting.

Second, patient satisfaction and healthcare utilisation are chosen as primary outcomes, since these factors are considered most relevant from the perspective of patient and society. Third, for the secondary outcome ‘patient empowerment’, so far, no uniform definition and no unique measurement tools exist. Therefore, we chose to use two validated questionnaires (GSE and Pearlin Mastery Scale) to estimate the effect of our intervention on patient empowerment. Although in previous intervention studies during cancer treatment comparable numbers of questionnaires were acceptable, the use of several questionnaires might induce loss to follow-up.

Last, we had to choose between random assignment at the patient or the caregiver level. We chose to randomise on patient level, using type of cancer and hospital for weighed randomisation, to ensure optimal comparison of study arms. To minimize the chance of contamination, GPs are only personally informed about the study details after one of their patients is randomised to the intervention. Given the low incidence of cancer in general practice (about 3 new patients meeting our inclusion criteria annually in an average general practice), we accepted the low chance of contamination resulting from the situation were one GP will first have a patient who is randomised to the intervention arm, followed by a patient randomised to the control arm.

### Trial status

The recruitment of participants started in April 2015. Patient inclusion will be completed in the first half of 2017. Patient follow-up is completed 1 year after the last patient will have been included.

## Abbreviations

DS-14: Type D Scale-14
EORTC QLQ-c30: European Organisation for Research and Treatment of Cancer Quality of life Questionnaire
EORTC-info 26: European Organisation for Research and Treatment of Cancer Assessment Satisfaction with information
EORTC-IN-PATSAT: European Organisation for Research and Treatment of Cancer Satisfaction with care questionnaire
GP: General practitioner
GSE: General Self-Efficacy Scale
HON: Home care oncology nurse
iMTA MCQ: Medical cost questionnaire of the institute for medical technology assessment
iMTA PCQ: Productivity cost questionnaire of the institute for medical technology assessment
MHI-5: Mental health inventory
NRS: Numeric rating scale
PEPPI: Perceived efficacy in patient-physician interactions
SDM-Q9: Shared decision making questionnaire
